## Abstract

**Background:**

Bacterial infection is a major cause of mortality in patients with cirrhosis. Spontaneous bacterial peritonitis (SBP) is a serious and common infection in patients with cirrhosis and ascites. Secondary prophylactic antibiotic therapy has been shown to improve outcomes after an episode of SBP but primary prophylaxis to prevent the first episode of SBP remains contentious. The aim of this trial is to assess whether primary antibiotic prophylaxis with co-trimoxazole improves overall survival compared to placebo in adults with cirrhosis and ascites.

**Methods:**

The ASEPTIC trial is a multicentre, placebo-controlled, double-blinded, randomised controlled trial (RCT) in England, Scotland, and Wales. Patients aged 18 years and older with cirrhosis and ascites requiring diuretic treatment or paracentesis, and no current or previous episodes of SBP, are eligible, subject to exclusion criteria. The trial aims to recruit 432 patients from at least 30 sites. Patients will be randomised in a 1:1 ratio to receive either oral co-trimoxazole 960 mg or an identical placebo once daily for 18 months, with 6 monthly follow-up visits thereafter (with a maximum possible follow-up period of 48 months, and a minimum of 18 months). The primary outcome is overall survival. Secondary outcomes include the time to the first incidence of SBP, hospital admission rates, incidence of other infections (including *Clostridium difficile*) and antimicrobial resistance, patients’ health-related quality of life, health and social care resource use, incidence of cirrhosis-related decompensation events, liver transplantation, and treatment-related serious adverse events.

**Discussion:**

This trial will investigate the efficacy, safety, and cost-effectiveness of co-trimoxazole for patients with liver cirrhosis and ascites to determine whether this strategy improves clinical outcomes. Given there are no treatments that improve survival in decompensated cirrhosis outside of liver transplant, if the trial has a positive outcome, we anticipate widespread adoption of primary antibiotic prophylaxis.

**Trial registration:**

ClinicalTrials.gov NCT043955365. Registered on 18 April 2020. Research ethical approval was granted by the Research Ethics Committee (South Central – Oxford B; REC 19/SC/0311) and the Medicines and Healthcare products Regulatory Agency (MHRA).

## Administrative information

Note: The numbers in curly brackets in this protocol refer to the SPIRIT checklist item numbers [1]. The order of the items has been modified to group similar items (see http://www.equator-network.org/reporting-guidelines/spirit-2013-statement-defining-standard-protocol-items-for-clinical-trials/).

**Table Taba:** 

Title {1}	ASEPTIC: Primary Antibiotic prophylaxis using co-trimoxazole to prevent SpontanEous bacterial PeritoniTIs in Cirrhosis—study protocol for an interventional randomised controlled trial
Trial registration {2a and 2b}	EudraCT # 2019–000,581-38 IRAS: 262,176 REC # 19/SC/0311
Protocol version {3}	Version 5.0, 20^th^ August 2021
Funding {4}	National Institute of Health and Care Research (NIHR) HTA grant number 17/67/01. No other external funding.

Role of sponsor {5c}	University College London (UCL) is the trial sponsor and has delegated the sponsor responsible for the overall management of the ASEPTIC trial to the UCL Comprehensive Clinical Trials Unit (CCTU). Specific functions delegated to the UCL CCTU include a clinical project manager at UCL CCTU overseeing the trial manager, who will be responsible for the day-to-day management of the trial and providing support to the site staff. The CCTU will be involved in approaching sites, initiation visits, case report form development, database construction, and protocol and patient information development in collaboration with the Trial Management Group (TMG), Independent Data Monitoring Committee (IDMC), and Trial Steering Committee (TSC).

## Introduction

### Background and rationale {6a}

For patients with advanced liver disease, bacterial infection is a major cause of morbidity and mortality. In patients with cirrhosis and ascites, spontaneous bacterial peritonitis (SBP) is the most common serious infection [2, 3], and secondary prophylaxis with antibiotic therapy is routinely prescribed to prevent further infection in patients who recover from SBP [4–6]. Yet, despite 90% of SBP cases presenting in patients with no previous episode [7], there is considerable uncertainty regarding the use of antibiotic therapy to prevent SBP in patients with ascites and no history of SBP, primary prophylaxis. An episode of SBP triggers a long-term reduction in survival and quality of life in cirrhosis, and therefore, primary prophylaxis to prevent this in the first place may actually offer greater gain than secondary.

Studies have shown that patients with ascites who have a low protein content (< 1.5 g/dL) were associated with a higher risk of developing infection [8–10], possibly due to reduced host opsonisation activity [8, 11, 12]. However, more recently, 2 large-scale, post hoc analyses showed no association between low protein count and increased SBP risk [13, 14]. Both the National Institute of Health and Care Excellence (NICE) and the European Association for the Study of the Liver (EASL) recommend antibiotic prophylaxis with quinolones for patients with ascitic fluid concentration < 1.5 g/dL, but the evidence to support this is limited and dated [6, 15, 16]. The American Association for the Study of Liver Disease (AASLD) recommends primary prophylaxis (with norfloxacin or co-trimoxazole) only if the ascitic protein is < 1.5 g/dL in the presence of impaired renal function and liver failure (Child–Pugh score > 9 and bilirubin > 3 mg/dL), which accounts for very few patients [17]. Conversely, the British Society of Gastroenterology (BSG) limits its guidance on primary prophylaxis due to a lack of consensus [18].

With support from the BSG trial development group, we conducted a national survey on the use of primary prophylaxis for SBP, and responses were received from 23 NHS Trusts (unpublished data). Nine centres reported routine use of antibiotics for primary prophylaxis against SBP; for 7 other centres, this was not routine practice, and the remaining 7 reported variable practice differing between clinicians. Evidently, there is considerable uncertainty and therefore great need for robust evidence to guide primary prophylaxis, especially for patients with ascites and ascitic protein > 1.5 g/dL and less advanced liver disease, and regarding the optimal duration of therapy. This is important as no therapies exist that prolong life in these patients outside of liver transplantation, which only occurs in a minority [19, 20].

### Objectives {7}

The primary objective of this trial is to assess the effect of primary antibiotic prophylaxis with co-trimoxazole on overall survival compared to placebo in adults with cirrhosis and ascites, utilising a treatment policy estimand. Key secondary objectives include assessing the incidence of SBP, hospital admissions, *Clostridium difficile* (*C. difficile*)-associated diarrhoea and antimicrobial resistance, cost-effectiveness, and incidence of cirrhosis-related events, liver transplantation and treatment-related serious adverse events.

### Trial design {8}

This is a multicentre, randomised, phase 3a, placebo-controlled, double-blind clinical trial. The trial design is displayed in Fig. 1. Patients with cirrhosis and ascites receiving care from at least 30 NHS hospital specialist liver services will be screened using the inclusion and exclusion criteria. We plan to recruit 432 eligible consenting patients that will be allocated in a 1:1 ratio to receive either co-trimoxazole or an identical placebo for 18 months, with a 3-monthly follow-up during this period. Thereafter, post-treatment follow-up will be 6-monthly until the end of the trial, and the maximum possible trial duration for any individual is 48 months.

**Fig. 1 Fig1:**
[figure not shown]
ASEPTIC trial schema

## Methods: participants, interventions, and outcomes

### Study setting {9}

The trial will take place in the UK at secondary or tertiary care NHS hospitals that frequently manage patients with advanced liver disease. A list of study sites can be found in the Appendix. Patients with cirrhosis and ascites who have been admitted to an inpatient hospital ward or who are attending hospital for an outpatient clinic appointment (including liver transplant waiting list clinics) or abdominal paracentesis on day-case units, will be identified and approached and asked to participate. The nursing and medical staff on the clinical trial team will be appropriately qualified to manage patients with complications of cirrhosis as for routine clinical care.

### Eligibility criteria {10}

The inclusion and exclusion criteria for patient eligibility are listed in Table 1.

**Table 1 Tab1:** Eligibility criteria for ASEPTIC trial

Inclusion criteria	Exclusion criteria
Patients with cirrhosis of Child–Pugh class B or C and the presence of ascites requiring any diuretic treatment or at least one or more paracentesis within 3 months prior to enrolment	Patients with current or previous SBP (defined as ascitic polymorphonuclear count > 250 cells/mm^3^ with either positive or negative ascitic fluid culture without an evident intra-abdominal surgically treatable source of infection; a white cell count > 500 cell/mm^3^ or positive microbial culture may be considered as evidence of previous SBP if the site PI considers this was in the context of a likely clinical diagnosis of SBP)
At least 18 years of age	Patients receiving palliative care with an expected life expectancy of < 8 weeks
Documented informed consent to participate	Allergy to co-trimoxazole, trimethoprim, or sulphonamides
	Pregnant or lactating mothers
	Patient enrolled in a clinical trial of investigational medicinal products (IMPs) that would impact their participation in the study
	Patients with serum potassium > 5.5 mmol/L related to pre-existing kidney disease which cannot be reduced^a^
	Patients receiving antibiotic prophylaxis (except rifaximin)^a^
	Patients with long-term ascite drains^a^
	Women of child-bearing potential and males with a partner of child-bearing potential without effective contraception for the duration of the trial treatment
	Patients with pathological blood count changes^a^: haemoglobin < 70 g/L, granulocytopaenia defined as absolute neutrophil count < 500 cells/µL, and/or severe thrombocytopaenia with platelets < 30 × 10^9^/L
	Patients with severe renal impairment, with eGFR < 15 mL/min
	Patients with skin conditions: exudative erythema multiforme, Stevens-Johnson syndrome, toxic epidermal necrolysis, and drug eruption with eosinophilia and systemic symptoms
	Patients with congenital conditions: congenital glucose-6-phosphate dehydrogenase deficiency of the erythrocytes and haemoglobin anomalies such as Hb Köln and Hb Zürich
	Patients with acute porphyria
	Any clinical condition which the investigator considers would make the patient unsuitable for the trial

^a^It is common for these investigations to change in patients with cirrhosis, and long-term ascitic drains may be removed. Patients may be rescreened for eligibility if this occurs

Originally, ascitic protein < 2 g/dL was proposed as an inclusion criterion for this trial; however, in the pilot phase, we found a low number of cases of low ascitic protein (38 out of 224 patients), despite only screening patients with refractory ascites and advanced liver disease. Also, there are no large-scale UK data concerning ascitic protein values and the use of ascitic protein in stratifying SBP risk remains contentious [13, 14]. Since it is well recognised that all patients with cirrhotic ascites are at high risk of bacterial infection, it was decided to change the inclusion criteria to persistent ascites without the need for an ascitic protein level. The intention of this amendment was to both increase the number of eligible patients for recruitment and still include patients at the greatest risk of SBP mortality. At the time of this amendment, 15 patients had been recruited. Sub-group analysis will be performed to examine the outcomes in patients with an ascitic protein content ≥ and < 2 g/dL.

The original eligibility requirement regarding the presence of ascites included the condition “despite 3 months of standard treatment”. Feedback from our sites described this time period requisite as a significant limitation to recruitment, and this was formally amended to “patients with cirrhosis of Child–Pugh class B or C and the presence of ascites requiring any diuretic treatment or at least one or more paracentesis within 3 months prior to enrolment”. This enables the recruitment of patients hospitalised with ascites shortly prior to their discharge.

### Who will take informed consent? {26a}

A participant information sheet (PIS) will be given to and discussed with potential patient recruits before consent is sought. Written informed consent will be obtained by appropriately qualified nursing or medical staff who are delegated at each site and have received protocol-specific training.

### Additional consent provisions for collections and use of participant data and biological specimens {26b}

Eligible patients who give their written informed consent will be investigated with baseline blood tests, ascitic fluid sample for white cell count and/or protein level, and pregnancy test if applicable.

### Interventions

#### Explanation for the choice of comparators {6b}

Co-trimoxazole was chosen as the antibiotic for this trial because it has an existing evidence base in SBP prophylaxis and is well tolerated and inexpensive [21–25]. There is a substantial literature on its use to prevent infection in patients living with human immunodeficiency virus (HIV) in resource-poor settings and little evidence of emergent microbial resistance to it [26–28]. Quinolones (e.g. ciprofloxacin or norfloxacin) were also considered as these have been shown to be effective in 2 meta-analyses that included primary prophylaxis trials to reduce the risk of SBP and mortality [4, 5], and they are commonly prescribed for secondary prophylaxis against SBP [15]. However, norfloxacin is not available in the UK, and other systemically absorbed quinolones have been associated with significant rates of antimicrobial resistance and *C. difficile* diarrhoea [29–34]. Rifaximin was not chosen because of its higher cost and widespread use for hepatic encephalopathy in the UK, which would have limited the number of eligible patients and/or risked significantly confounding analyses.

Current EASL guidance (2018) states that norfloxacin prophylaxis should be stopped in patients with long-lasting improvement of their clinical condition and disappearance of ascites but includes no guidance on the duration of therapy in those with persisting ascites [15]. Our trial treatment period of 18 months will test whether there is a beneficial effect on mortality, if there is a waning in efficacy over time, and whether the intervention impacts antimicrobial resistance.

The comparator is placebo, which is an acceptable option as there is no UK consensus regarding the necessity for prescribing primary prophylaxis in SBP and the majority of clinicians who responded to our national survey did not routinely do so.

#### Intervention description {11a}

The investigational medicinal product (IMP) is either one capsule of co-trimoxazole 960 mg once daily or an identical capsule containing placebo once daily. A bottle containing the IMP will be dispensed to patients via the clinical trials pharmacy department at their respective sites to coincide with randomisation and as close to the patient’s 3-monthly follow-up visits as possible. Patients will be instructed to start taking the IMP either as close to the randomisation date as possible (for those recruited in an outpatient setting) or on discharge from the hospital (for those recruited as inpatients).

#### Criteria for discontinuing or modifying allocated interventions {11b}

The IMP may be temporarily stopped if the patient experiences any severe adverse reactions or if, in the opinion of the site principal investigator (PI) or delegate, it is necessary. The patient will be encouraged to remain in the trial and continue to attend follow-up visits. The patient may be re-challenged following stopping of the intervention for at least a week if the PI or delegate considers this safe. The IMP will be adjusted in the following specific scenarios:

Renal dysfunction: if eGFR falls to < 30 mL/min whilst taking the IMP, dosing will be reduced to one capsule on alternate days and will be increased back to one capsule once daily If eGFR returns to > 30 mL/min. If eGFR reduces to < 15 mL/min whilst taking the IMP, it will be stopped. If the eGFR returns to > 15 mL/min but remains < 30 mL/min, the IMP will be restarted at alternate day dosing but will not be increased to once-daily dosing.Hyperkalaemia: if serum potassium rises to ≥ 6 mmol/L, the IMP will be stopped and re-introduced when the site PI considers it safe. If hyperkalaemia ≥ 6 mmol/L occurs twice or more whilst taking the IMP, it will be reduced to alternate day dosing on re-introduction for the remainder of the study.Thrombocytopaenia: if the platelet count falls to < 50 × 10^9^/L with active bleeding, to < 30 × 10^9^/L without active bleeding, or in a manner that concerns the PI or clinical team regarding increased risk of bleeding, the IMP will be stopped until counts are ≥ 30 × 10^9^/L, any bleeding has resolved, and it is deemed safe to do so.Non-SBP-related hospital admission: the IMP should be stopped upon admission to the hospital and restarted when safe to do so, on or soon after discharge.Recovery from ascites: if ascites resolves for > 6 months without diuretic medications, patients will stop taking the IMP as their health status has improved.

The IMP will be stopped in the following scenarios:

Stevens-Johnson syndrome.Hospital admission with SBP. As per routine clinical practice, patients will be commenced on long-term antibiotics as secondary prophylaxis following treatment of SBP.Any significant medical reason deemed by the local PI.Any suspected unexpected serious adverse reaction (SUSAR) event.

Every effort will be made to ensure patients withdrawn from the trial treatment continue to be followed up as per the protocol until the trial end.

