#### Relevant concomitant care permitted or prohibited during the trial {11d}

Concomitant care with long-term antibiotic prophylaxis is not permitted, except for rifaximin prescribed for hepatic encephalopathy. Patients will be stratified according to their use of rifaximin at randomisation and whether they are presently on the waiting list for a liver transplant. As hyperkalaemia is a known potential side effect of co-trimoxazole, caution will be taken in patients taking other medications that can cause hyperkalaemia: ACE inhibitors, angiotensin receptor blockers, and potassium-sparing diuretics. Patients at increased risk of renal dysfunction and/or hyperkalaemia, namely those with existing kidney dysfunction and those taking spironolactone or amiloride, are not eligible if the PI judges this risk cannot be managed with the adjustment of diuretics.

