^c^Blood tests should include full blood count, with haemoglobin, white cell count, platelets, INR (or prothrombin time converted to INR), sodium, potassium, serum creatinine, and urea. Liver function tests should include albumin, alanine aminotransferase (ALT), alkaline phosphatase, and bilirubin. Renal function tests including eGFR

^d^At each indicated visit, one bottle of 100 capsules of trial medication is dispensed to the patient (either co-trimoxazole or placebo capsules)

^e^Visit 2 is to monitor the safety of the patient and to make any dose modifications to concomitant medications if needed

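### Patients entering with eGFR 15 to 29 have once daily as their only stated regimen, although the plan's own renal rule doses that range on alternate days

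*Protocol article*

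**What the plan says.** All references are to the protocol article.

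- **Entry.** The renal exclusion in Eligibility criteria {10}, Table 1, reads "Patients with severe renal impairment, with eGFR < 15 mL/min". No other listed criterion sets a higher eGFR limit. Under Relevant concomitant care {11d}, patients with existing kidney dysfunction, among others at raised risk of renal dysfunction or hyperkalaemia, "are not eligible if the PI judges this risk cannot be managed with the adjustment of diuretics".
- **Starting regimen.** Intervention description {11a} gives "one capsule of co-trimoxazole 960 mg once daily or an identical capsule containing placebo once daily". The Abstract gives the same regimen. Neither mentions a renal variant.
- **Dose by renal function.** Criteria for discontinuing or modifying allocated interventions {11b} says that "if eGFR falls to < 30 mL/min whilst taking the IMP, dosing will be reduced to one capsule on alternate days", with a return to once daily above 30 and a stop below 15. If eGFR then recovers to a value between 15 and 30, "the IMP will be restarted at alternate day dosing but will not be increased to once-daily dosing".
- **What is measured.** Table 2 schedules blood tests at screening and again at day 10, month 3 and every 3 months to month 18. Footnote c includes "Renal function tests including eGFR".

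**The concern.** The plan treats an eGFR of 15 to 29 as a range that calls for half the usual dosing frequency, both when a patient drops into it and when a patient climbs back into it. Entry is open across the same range, but the rule's wording does not reach a patient who is already there at randomisation. Such a patient has not had a fall while on the drug and has not been stopped and restarted.

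Section {11d} itself names patients with existing kidney dysfunction as being at increased risk of further renal dysfunction or hyperkalaemia. On a literal reading, some of them would start on twice the dosing that the plan sets for their level of renal function. Sites could also read the clause differently, so that two similar patients receive different doses at different centres.

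**Working it through.** The plan gives no figure to reproduce. The check sets the rules side by side and then does simple dose arithmetic.

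**Step 1. Map eGFR to the stated dose.**

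| Situation | eGFR below 15 | eGFR 15 to 29 | eGFR above 30 | Source |
|---|---|---|---|---|
| At entry | excluded | eligible; once daily is the only regimen stated | once daily | {10} Table 1, {11a} |
| Fall while on the IMP | stop | alternate days | once daily | {11b} |
| Restart after a stop below 15 | remains stopped | alternate days, once daily barred | once daily | {11b} |

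The middle column is inconsistent. The same renal function leads to once daily in the first row and alternate days in the other two.

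**Step 2. Look for another rule that sets a reduced starting dose.**

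- The investigator's judgement in {11d} decides who enters, and the tool it names is diuretic adjustment. It sets no dose of trial drug.
- The investigator's general power in {11b} is to pause, stop or re-challenge. Alternate-day dosing appears only under the renal rule and the recurrent-hyperkalaemia rule.
- Table 2, footnote e, describes day 10 as a safety visit with dose changes to concomitant medication. It does not mention the trial drug.

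None of these gives a starting dose for an entrant at 15 to 29.

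**Step 3. Size per affected patient.** Weekly dose = capsules per week × 960 mg.

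- Once daily: 7 × 960 = 6,720 mg.
- Alternate days: 3.5 × 960 = 3,360 mg.
- Ratio: 6,720 / 3,360 = 2.

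If a site treated a day-10 value below 30 as triggering the rule, the excess before correction would be about 10 − 5 = 5 capsules, or 5 × 960 = 4,800 mg.

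**Step 4. Who is exposed.** Patients are "allocated in a 1:1 ratio to receive either co-trimoxazole or an identical placebo for 18 months", so extra active drug arises in only about half of the entrants concerned. The share entering at 15 to 29 is not stated. For scale only, assume 0.5% to 3% of the planned 432:

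- 0.005 × 432 = 2.2 entrants, of whom about 1.1 are on co-trimoxazole.
- 0.03 × 432 = 13.0 entrants, of whom about 6.5 are on co-trimoxazole.

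Nothing in the document anchors that range, and the point does not depend on it.

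**The case against.** The strongest reply is that this is a gap in a condensed article. A renal-adjusted starting dose is the kind of prescribing detail that a full protocol or pharmacy instruction holds, and the full protocol is not shown. Section {11b} is by its title about modifying treatment, so wording tied to patients already on the drug is natural. Section {11a} describes the standard regimen and does not direct once-daily dosing at eGFR 20. A sensible prescriber who sees a screening eGFR of 20 would probably apply the below-30 rule from the first dose. There are also safeguards: the investigator's entry judgement, the unsuitability criterion, the potassium limits, the stop below 15 and regular blood tests from day 10.

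Much of this stands, and it keeps the point minor. It does not remove it. The article sets out the renal rule branch by branch (fall, recovery, stop, partial recovery) and also states the entry limit and the regimen. Taken together, these statements give the less cautious dose to a patient already in the range. The safeguards depend on discretion or act later, and none sets the starting dose.

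Two stronger readings are tempting, and the document supports neither.

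- A reader might multiply the weekly difference over the full 18 months and present the total as the excess exposure. That would need eGFR to stay at 15 to 29 throughout, with full adherence, no death, no pause for admission (which {11b} requires for non-SBP admissions) and no action after any of seven scheduled blood tests from day 10 to month 18. The Discussion describes a population with high rates of complications, admissions and mortality.
- A reader might infer that the survival comparison is compromised. Nothing in the document shows that. The number affected is unknown, and the same capsule rules apply in both arms.

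**Conclusion.** The inconsistency holds as a minor dosing and safety point, with medium confidence. Entry is open at eGFR 15 to 29, once daily is the only regimen stated, and the alternate-day rule for that range is worded only for a fall on treatment or a restart. For an entrant who stays at about 20, the literal result is 7 rather than 3.5 capsules a week. On co-trimoxazole that is 6,720 mg rather than 3,360 mg, twice what the renal rule would give.

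This rests on a literal reading of the article and on the full protocol having no starting-dose rule for this range, which cannot be checked here. How many patients are affected, and for how long, cannot be derived from the document. The sample size and the primary analysis are untouched.

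**What to change.** First check whether the full protocol or the pharmacy instructions already give a starting dose for eGFR 15 to 29. If they do not, reword the trigger in {11b} along these lines: *if the most recent eGFR before the first dose, or any eGFR while on the IMP, is < 30 mL/min, dose one capsule on alternate days.* Keep the stop below 15 and the return to once daily above 30.

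The most recent value should be used rather than the screening value by default. Table 2 allows screening up to 12 weeks before randomisation, and inpatients start treatment only on or after discharge, so the screening result can be out of date by the first dose.

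The cost is one clause and a note to sites. No new scheduled visit or test is needed, because eGFR is already in the screening bloods and any later routine result can be used. The rule would apply equally to both arms, so blinding is unaffected. The downside is a lower starting dose in what is probably a small subgroup. The article describes recruitment as ongoing, so the change could still help later entrants.
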